### Preclinical validation studies of amygdala deep brain stimulation in post-traumatic stress disorder

Based on the foregoing, it is predicted that high-frequency DBS of the BLn will reduce the symptoms of PTSD. We tested this hypothesis in a rat model using inescapable shocks. Inescapable shocks in rats produce long-lasting behavior changes that mimic PTSD[127]. Mikics and colleagues[128] demonstrated that rats traumatized by inescapable shocks, in the presence of a conspicuous object, had the tendency to bury the object when re-exposed to it 28 days later. Burying behavior does not occur normally in rats. The behavior models PTSD faithfully in that it is maintained over several weeks without signs of extinction, it is generalized to other objects than the one originally presented and the rats also displayed sustained social avoidance[128]. The behavior is robust and the majority of rats will have buried the object completely at the end of a 10-minute observation period, making this model attractive for studies.

We conducted two rodent studies using this PTSD model and high-frequency BLn DBS as a treatment. In the first study[129], we showed that DBS of the right BLn corrected the object-burying behavior following inescapable shocks in rats. The difference in behavior was striking. The sham control rats spent on average 13 times more time burying the ball than the DBS-treated rats (*P* <0.005), while the latter spent 18 times more time exploring the ball. In the second study, we showed that BLn DBS, but not paroxetine, reduced burying behavior following inescapable shocks[130]. In that study, we used a crossover design with real versus sham DBS, each administered for one week. We demonstrated that 1) BLn DBS was effective at one week, and the effects persisted after another week of sham treatment, and 2) BLn DBS was efficacious when the initiation of the therapy was delayed for a week after establishment of the behavior, modeling chronic PTSD. In addition we tested whether the effect of DBS on ball burying behavior was due to a general pattern of behavioral inhibition. This was assessed using the elevated plus maze, a model for assessing general anxiety, following the last burying behavior evaluation at 14 days. Rats treated with paroxetine spent significantly more time in the open arms, suggesting a reduction in general anxiety. The animals treated with DBS showed no significant difference. These results suggest that paroxetine carries its therapeutic effects on PTSD through a nonspecific reduction in general anxiety, while DBS improves PTSD without such nonspecific anxiety-reducing effects. The DBS-treated rats did not exhibit signs of fearlessness or carefree behavior during the trial. The animals treated with DBS in this study also did not display abnormal or violent behavior.

Other preclinical studies[131, 132] have reported that DBS of the amygdala and the hippocampus respectively raised the threshold for electroconvulsion, therefore leading to protection against seizures. In humans, chronic high-frequency stimulation of mesiotemporal structures has been shown to raise the seizure threshold. Velasco *et al*.[133] reported that the chronic high-frequency stimulation of the normal or the sclerotic hippocampus reduce the incidence of seizures in refractory epileptic patients without causing side effects. Patients with normal hippocampus had a 95% seizure reduction; patients with a sclerotic hippocampus had 50 to 70% seizure reduction.

### Prior findings with amygdala neurosurgery in humans

In stereotactic amygdalotomy, destructive lesions are created in both amygdalae using radiofrequency ablation for patients suffering from intractable aggression. The procedure was performed primarily in the 1960’s and the 1970’s. Narabayashi[134] introduced the stereotactic amygdalotomy in the 1960’s. Initially, the procedure was offered to patients suffering from epilepsy or EEG abnormality in addition to aggressive behavior, but eventually it was offered more broadly to patients suffering from ‘intractable aggression’. Following this initial report, several other authors reported their outcomes for the treatment of aggression and over a thousand patients have been treated[135–137]. The overall improvement in symptoms reported range between 33 and 100%, with most authors reporting 70 to 85% improvement[138]. Lee and colleagues (1998)[139] reported two patients who underwent stereotactic amygdalotomy for intractable aggression and demonstrated specifically reduced behavioral and autonomic ‘fight or flight’ activation in response to stressful cues. In these reports of stereotactic amygdalotomy, the amygdala was safely approached through a transfrontal trajectory by many investigators. Large lesions were created using wax, ethanol, or radiofrequency ablation with the goal of complete destruction of bilateral amygdala. The size of those lesions was approximately 10 to 20 times the diameter of the current DBS electrode. Despite the large lesions, in his series of 60 patients, Narabayashi *et al*.[134] observed no psychological disturbance from the procedure and only one case of transient weakness that resolved after 3 weeks. In another series, Kiloh and colleagues[140] reported seven complications following 18 operations. There were four cases of new-onset epilepsy and three cases of hypersexual behavior. The epilepsy resolved over a period of several months. Since those reports, surgical and imaging techniques have evolved considerably. Thus, no complications were reported in a more recent study where modern stereotactic and ablative techniques were used[139].

Since the advent of DBS, destructive procedures, such as subthalamotomy and thalamotomy to treat Parkinson’s disease and tremor have become obsolete. This has occurred because the safety profile of DBS is superior to destructive strategies. With minimal disruption of the cerebral tissue, the risks of hemorrhage, stroke and neurological deficits are significantly reduced. In addition, neuromodulation is reversible and side effects can often be corrected with programming changes.

There is a case report of inadvertent DBS of the main amygdala output, the stria terminalis[141]. A patient underwent the placement of bilateral globus pallidum interna (GPi) DBS electrodes (model 3387, Medtronic, MN, USA) for the treatment of dystonia. There was improvement in dystonia at the 4-month follow-up visit. Apparently soon thereafter, the left-sided electrode inadvertently migrated to the area of the stria terminalis, the major white matter tract output from the amygdala. The left electrode delivered stimulation at the following parameters: 2.7 V (amplitude), 180 μsec (Pulse width) and 180 Hz (frequency). Over the next five months, the patient developed symptoms of depression, apathy, irritability, hopelessness, and suicidality. Once the electrode was repositioned, the patient’s symptoms resolved completely. His neuropsychological condition remained unchanged from preoperative assessments through 9 total months of stimulation.

DBS of white matter tracts, like the stria terminalis, is known to cause an increase of the activity of the tract and its neuronal targets. This phenomenon commonly leads to DBS side-effects such as muscular contractions, which are due to internal capsule (white matter tract) stimulation, or diplopia, from oculomotor nerve stimulation (also white matter). In essence, DBS of the stria terminalis equates to the state of amygdala overactivity seen in PTSD patients. On the contrary, gray matter DBS has been shown clinically and by functional neuroimaging to reduce the metabolic activity of surrounding areas and neuronal targets[73]. Therefore, DBS of gray matter, such as the BLn, would likely have effects opposite those seen from DBS of the white matter in the case of the amygdala. This case is critical for several reasons:It supports the model that amygdala overactivity is responsible for the symptoms of PTSD. DBS of the stria terminalis physiologically equates to amygdala overactivity. In this patient with no psychiatric history, an increase in amygdala output activity has led to symptoms commonly seen in combat PTSD (for example, irritability, helplessness, depression, and suicidality).The correction of the amygdala activity led to resolution of the symptoms. As opposed to DBS of the stria terminalis, BLn DBS is expected to reduce amygdala output.The patient did not suffer from a seizure or deterioration in neuropsychological status during chronic DBS for nine months. This suggests an acceptable safety profile of DBS of the amygdala.

Very recently, Sturm and colleagues[142] (2013) applied conventional DBS bilaterally to the BLn in a 13-year-old boy with intractable self-injurious behavior (SIB) in the context of mental retardation and Kanner’s autism. Over the course of 26 months follow-up at the time of publication, the authors described clinically significant improvement in SIB, as well as social communication and even language function; the child had not previously developed language and spoke for the first time beginning six months after DBS. Notably, only stimulation of the BLn, but not the central nucleus, the amygdala outflow tract, or neighboring regions affected by other contacts of the stimulating electrodes, led to benefit. Also important was the absence of significant side effects, including seizures. There was no benefit from insertion without stimulator activation, and an exacerbation occurred consequent to battery depletion with reinstatement of benefit after re-initiation of stimulation. Electrode insertion trajectory and stimulation parameters used in that single case correspond closely to those planned in the present investigation (transfrontal (Figure 1); 130 Hz, 120-μsec pulse width, 2 to 6.5-V amplitude).

**Figure 1 Fig1:**
[figure not shown]
**Transfrontal trajectory for deep brain stimulation of the basolateral amygdala.**

Electrical stimulation of the amygdala in humans has also been performed in patients undergoing depth electrodes for epilepsy monitoring[143–145]. The amplitude delivered to the tissue was up to 10 mA, several fold higher than the recommended DBS parameters. The smaller diameter of those electrodes compared to the current DBS implant also means that the charge density delivered was several times higher than the maximum allowed by the Medtronic Activa system we will use in this study. In addition, the frequency was kept low: between 5 to 10 Hz, approximately 10 to 20 times lower than currently used for movement disorders, and 20 to 30 times lower than planned in this investigation. These settings were meant to generate seizures or other symptoms that would be related to the amygdala. The authors were intrigued that very few patients reported significant anger despite the elevated settings of stimulation. In addition, few convulsions were noted despite the high-amplitude and the fact that the patients were suffering from medically refractory temporal lobe epilepsy[143]. In our protocol, the amygdala tissue disruption and the electrical charge density are both several folds (that is, 10 to 20 times) smaller than listed in previous reports concerning amygdala neurosurgery. Therefore, we expect our safety profile to be considerably better. In addition, we are benefiting from the advances in surgical and imaging techniques since those reports were published.

Taken together, the data reviewed in the preceding sections support the proposal that persistent amygdala hyperactivity, most likely localized to the BLn, underlies the symptoms of treatment-refractory combat PTSD; a treatment that would directly reduce this hyperactivity could benefit patients whose symptoms do not respond to standard treatments. High-frequency DBS of the BLn could do this without significant risk of causing seizures or other major behavioral changes. We recognize that, as in other neuropsychiatric disorders associated with dysfunction in limbic circuitry, amygdala hyperactivation in PTSD is likely a node in an interconnected circuit, comprising at least the vmPFC, anterior insula, and extended amygdala, as well as the ventral striatum, with reciprocal connections to thalamus and hypothalamus, and output to brainstem nuclei that are also involved in the clinical phenomenology seen in the condition. While we thus agree with other investigators[146] that the BLn is not the *only* potentially valuable target for DBS in PTSD, we believe, based on the rationale described above, that it is the optimal target and it can be modulated safely with current technology.

## Methods/Design

### Purpose and justification of the study

The purpose of the current study is to evaluate the safety and potential therapeutic benefit of the Medtronic Activa DBS system implanted bilaterally in the BLn of the amygdalae in combat veterans with severe, chronic, treatment-resistant PTSD. DBS is considered a safe, nondestructive, and reversible therapy for neurological and psychiatric conditions. Despite being safe, DBS carries risks related to the surgery as well as risks associated with the neuromodulation. We expect the rate of complications from the amygdala BLn implantation procedure to be comparable to reported risks in other DBS applications, as reviewed elsewhere[147] and as detailed below.

Characterizing potentially undesirable effects of chronic high-frequency DBS of the amygdala is a principal aim of the study. While we expect there to be a low risk of serious adverse effects, the study involves extensive monitoring for psychiatric, neurologic, and neuropsychological adverse effects as described below and listed in Additional file1.

The duration of the investigation will be 24 months for each subject following device implantation and randomization. The subjects will be followed biannually once they exit the protocol. The presence of a significant other engaged in the healthcare of the patient will assist in early detection of adverse effects, as well as evaluating functional benefits.

We believe the risks involved, and the burden of extensive repeated assessments, are justified because treatment-resistant PTSD is a very serious illness associated with significant suffering and morbidity. There are currently no good treatment options for patients who have failed to improve with psychotherapy and several lines of psychopharmacological agents. We believe that BLn DBS is a therapeutic option worth investigating.

### Design of the study

This proof-of-concept trial will follow a randomized and blinded staggered-onset design for the initial three months after implantation, followed by open-label active stimulation in all subjects for a total of 24 months after implantation, with systematic monitoring of safety and efficacy. This design has been used in other recent successful early clinical proof-of-concept trials of DBS in psychiatric conditions[148]. The staggered onset of active stimulation permits assessment of the possible effect of electrode insertions without stimulation (‘microlesioning’) of the amygdala target. We expect greater improvement in PTSD symptoms in patients with initial active DBS, compared with sham stimulation, and improvement in the subgroup initially randomized to sham after stimulators are subsequently activated. The comparison of sham to active stimulation also permits a direct comparison of possible adverse effects of BLn DBS to insertion of inactive electrodes. We feel that the 2-month delay in receiving active treatment for those subjects randomized to initial sham stimulation is justified based on the scientific value of the comparisons noted, given the previously untested nature of the intervention. For ethical and investigative reasons, all subjects will receive active stimulation beginning at three months after implantation. In both treatment-refractory OCD[72] and depression[81], the benefits of stimulation increased over a 1- to 2-year period after initiation, leading us to design this pilot study with a 2-year investigational period after implantation. Given the chronic nature of illness in the subjects to be included in this study, it also makes sense heuristically to expect optimal benefit to take up to 2 years to be manifest. Equally important is the potential for adverse effects of long-term amygdala DBS to build or change over time.

The study will be conducted at the VA Greater Los Angeles Healthcare System (GLA) facilities. Several key elements make GLA the optimal location to conduct this rigorous trial and insure the safety of the subjects: 1) GLA is one of only six VA Parkinson’s Disease Research, Education and Clinical Care (PADRECC) centers. As such, GLA routinely conducts DBS procedures for the treatment of movement disorders. In addition, the GLA staff has extensive experience with the conduct of human trials in DBS. They have successfully participated in several DBS trials, including the cooperative studies for Parkinson’s disease[149] and the recent SANTE trial for the treatment of epilepsy[150]. 2) GLA treats a large PTSD population and has state-of-the-art psychiatric treatment programs for combat PTSD. The staff has extensive experience with the treatment of complex chronic PTSD in an academically affiliated medical center (UCLA) with a variety of outpatient programs, including PTSD specialty clinics, outpatient mental health centers in six to eight different communities in the greater Los Angeles area, pain clinics, post-deployment clinics, and a domiciliary. Algorithms in place allow for the safe and efficient treatment of acute psychological deterioration or transient worsening, including inpatient psychiatry and neurosurgical services. 3) GLA is also one of the 16 VA Epilepsy Centers of Excellence (ECoE). As such, it possesses unique professional expertise and advanced telemetry equipment for the monitoring, treatment, and prevention of seizures and epilepsy. In addition, the team has extensive experience with telemetry-related research.

This is a pilot study and thus will involve only six subjects, two sets of three randomized to either staggered onset time of initiation of stimulation. We believe this subject number will adequately address the proof of concept purpose of the study and provide meaningful information about the difference between active and sham stimulation (see above).

The study will provide close follow-up of patients after DBS surgery by a team involving a functional neurosurgeon, psychiatrists, an epilepsy specialist neurologist, a neuropsychologist, a geriatric neuropsychiatrist, functional neuroimaging experts, and a clinical neurophysiologist, all with expertise in psychiatric neuroscience, clinical care of veterans with PTSD, and the use of DBS. Similar to other recent studies[73, 75, 151] and guided by consensus recommendations[152, 153], we intend to publish de-identified complete details of individual patient demographic and clinical descriptors, study procedures and results, neuroimaging procedures, and DBS implantation procedures and stimulation parameters.

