Potential subjects are recruited for the study via distribution of flyers to staff at GLA Mental Health Outpatient programs. Flyers include summarized inclusion and exclusion criteria. Potential subjects are informed about the study by their treating clinician, and given contact information for the study psychiatrist and neurosurgeon if they are interested. Charts of potential patients are then reviewed by investigators based on an IRB-issued Waiver of Consent for Screening. Patients meeting chart-review-based inclusion and exclusion criteria are invited to attend an in person assessment for further determination of eligibility. Eligible subjects will sign informed consent. After this, they will undergo baseline evaluations spaced over a six-week period, including neuropsychological testing and a baseline ^18^FDG PET scan (described below). Patients are reassessed with the Clinician Administered PTSD Rating Scale (CAPS[154]) at the end of this baseline period, and only those who maintain a total CAPS score ≥85 and other inclusion and exclusion criteria will be kept in the study. An additional baseline evaluation is stipulated by California Law referring to ‘Psychosurgery’ (WIC Sec 5326.6): all potential subjects must undergo examination by an independent team, consisting of neurosurgeons and psychiatrists uninvolved in the treatment or the study protocol, to ascertain capacity to consent, severity of illness, and inadequacy of response to standard treatments. This team of independent experts is assigned by the Medical Director of the Los Angeles County Department of Mental Health. Concomitant psychotropic medication regimens will be kept constant for the first six months of the study, unless medication-related adverse events, intercurrent medical conditions, or changes in psychiatric status make alterations clinically necessary.

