### Randomization and blinding

There will be two study groups, A and B, corresponding to either onset of active stimulation at 30 days or 90 days post-implantation. Prior to enrollment of the first patient, a computer algorithm will randomize each of the six potential subjects to either group A or B (three each), in blocks of two. After the 1-month post-implantation EEG telemetry session, the study neurophysiologist will learn the group assignment of each subject. Subjects and all other investigators will be blind to group assignment until completion of the trial.

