In this trial, we will use the device as it comes from the manufacturer. The surgical implantation of the device follows the same technique used for movement disorder surgeries. The stimulation parameters that will be used in this protocol are commonly used in movement disorder and therefore the energy demand on the device will be the same as typically used in movement disorders.Following the standard surgical procedure for DBS system implantation, the patients will undergo the placement of a Leksell (Elekta, Atlanta, GA, USA) stereotactic frame. The electrode trajectory will be planned using stereotactic software (BrainLab, Munich, Germany). We will follow a traditional transfrontal trajectory (Figure 1). The transfrontal trajectory to the amygdala is a well-documented procedure traditionally used for stereotactic amygdalotomy. We will implant the DBS electrodes bilaterally in the BLn. A curvilinear incision will be made bilaterally 3 cm lateral to midline and 1 cm in front of the coronal suture. A burr hole will be placed bilaterally with a high-speed drill for placement of a Stimloc device (Medtronic, Minneapolis, MN, USA) to hold the electrode in place. Once the Stimloc is attached with the two self-tapping screws, the dura will be opened. The dura will be coagulated back and the cortex exposed, coagulated, and pierced. The electrode 3387 (Medtronic, Minneapolis, MN, USA) will then be introduced down the cannula. All the contacts of the electrode will then be stimulated at incremental voltages up to 7 volts to confirm the absence of immediate side effects by the study neurophysiologist (SK) while the patient is awake and is being examined by the study psychiatrist (RK, HS) and neurosurgeon ([name]). The left electrode will be inserted and tested first for side-effects, and then, the right electrode will be inserted and tested. In the absence of serious adverse effects, the stimulators will be turned off and the electrodes will then be tunneled under the skin down to the upper chest area. They will be connected to a dual-channel pulse generator Activa PC (Medtronic, Minneapolis, USA).

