After surgery, patients will be kept in the hospital for approximately 3 days to ensure postoperative safety/stability. Then patients will return to the clinic for weekly safety evaluations for the first five months. Stimulators will be kept off in all patients for the first four weeks. Then, once the EEG telemetry session described below is complete, patients will be assigned randomly, in a double-blind fashion (only the study neurophysiologist will know) to have stimulation initiated at that 4-week postoperative time point, or after an additional 2 months (that is, 3 months postoperatively).

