The study includes two specific elements that hope to add to the understanding of brain-behavior relationships from our intervention. First, the double-blind staggered-onset sham-stimulation phase will allow us to observe changes associated with electrode implantation without electrical neuromodulation; what others have referred to as a ‘microlesioning effect’. This will also allow us to separate out nonspecific aspects of study involvement from specific effects of DBS. The study also includes prestimulation and poststimulation PET scanning sessions, each of which includes scans done before and after exposure to a trauma narrative as has been done in other functional neuroimaging studies of PTSD. We chose to use the ^18^FDG PET paradigm because it permits assessments of change in stimulus-driven functioning of the brain for longer time epochs than either ^15^O_2_ PET or fMRI. We feel that this more closely models the clinical difficulty patients with PTSD face; it is not just the nature and intensity of reactions, but their duration and ensuing effect on functioning that is important. We considered including a pre-implantation, as well as a pre-stimulation, post-implantation PET study. While this would be ideal from a scientific perspective, we decided that the additional patient burden was not justified given the completely uncharted territory of this pilot investigation.

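### All six subjects are implanted and only switch-on time is randomised, so the stagger cannot isolate the 'microlesioning' effect of electrode insertion

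*Protocol article*

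**What the plan says.** The protocol article makes the claim twice.

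- 'Design of the study': "The staggered onset of active stimulation permits assessment of the possible effect of electrode insertions without stimulation", glossed as microlesioning of the target. The same section rests the two-month delay for the sham group on the scientific value of its comparisons.
- Discussion: the blinded sham phase "will allow us to observe changes associated with electrode implantation without electrical neuromodulation", again named a microlesioning effect. The next sentence adds that the phase will separate general effects of taking part from effects specific to DBS.

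The design is described as follows.

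- Size and allocation ('Design of the study'): the trial "will involve only six subjects, two sets of three randomized to either staggered onset time of initiation of stimulation".
- Groups: "There will be two study groups, A and B, corresponding to either onset of active stimulation at 30 days or 90 days post-implantation" (section 'Randomization and blinding').
- Implantation ('Surgery and the deep brain stimulation system'): "We will implant the DBS electrodes bilaterally in the BLn". No unimplanted or sham-surgery comparator is described.
- Common off period (same section): "Stimulators will be kept off in all patients for the first four weeks".
- Selection on the outcome scale ('Participants'): after the six-week baseline, "only those who maintain a total CAPS score ≥85 and other inclusion and exclusion criteria will be kept in the study".

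'Data analysis' states that no formal treatment hypothesis is tested. 'Study aims' lists safety, the effect of DBS on symptoms and quality of life, and brain metabolism; an insertion effect is not among them.

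**The concern.** To assess the effect of inserting electrodes, a trial needs a comparison in which insertion differs and the rest does not. Here insertion never differs between subjects. The stagger creates a comparison of stimulation on with stimulation off, among people who all have electrodes in place.

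At stake is how the off period is read. If CAPS falls after surgery while the stimulators are off, the text invites the reader to see a biological effect of the electrode track. The same fall could come from having had brain surgery in a first-ever trial, from weekly contact with the team, from the natural course, or from selection at a high score. A mechanistic conclusion drawn from it could carry into the design of the next study without support from this one.

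**Working it through.** The article gives no figure on this point, so there is nothing to reproduce. The check is whether the design can identify the effect.

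**Model.** For each subject and month let the expected score be

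μ + I·(implanted) + N·(after implantation) + S·(stimulator on),

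where I is the insertion effect, N collects non-specific response, time and regression to the mean, and S is the stimulation effect. The schedule gives:

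| Time | Group | I | N | S |
|---|---|---|---|---|
| Baseline | A and B | 0 | 0 | 0 |
| Month 1, before switch-on | A and B | 1 | 1 | 0 |
| Months 2 and 3 | A | 1 | 1 | 1 |
| Months 2 and 3 | B | 1 | 1 | 0 |
| Month 4 | A and B | 1 | 1 | 1 |

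**Result.** The I and N columns are identical. With the intercept, the design matrix has rank 3 for 4 parameters.

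- Randomised contrast, months 2 and 3: A − B = (μ + I + N + S) − (μ + I + N) = S. Stimulation is estimable; insertion has cancelled.
- Off-period change from baseline: (μ + I + N) − μ = I + N. Only the sum is estimable, from six subjects to about day 30 and three to day 90.
- Letting N take a different value each month does not help: the I column is then the sum of the monthly N columns.
- Adding a concurrent unimplanted group on the same schedule would raise the rank to 4 of 4, if N is shared. Even then, placebo response to surgery would stay mixed with I unless that group had sham surgery.

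More subjects would not change this. Nor does it depend on the test stimulation given at surgery and telemetry: it would hold with none.

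**Size of one component.** Regression to the mean can be sized, but only with assumed inputs, because the article gives no CAPS mean, SD or reliability. Each score was simulated as a true score, normal with variance r·SD², plus independent error with variance (1 − r)·SD². Subjects were kept if two scores were at least 85, and the second was compared with a third (the article does not say which baseline CAPS is the reference). Assumed ranges: mean 75 to 95, SD 12 to 18, reliability r 0.7 to 0.9; one million draws per setting.

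- Two screens at 85: mean fall of 0.3 points (mean 95, SD 12, r 0.9) to 4.1 points (mean 75, SD 18, r 0.7; from 98.5 to 94.4).
- One screen at 85: 0.4 to 6.3 points.

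The repeat screen shrinks the effect but does not remove it. For scale, a 30% response from a baseline of 85 is 0.30 × 85 = 25.5 points. Nothing in the article allows placebo response or natural course to be sized.

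**The case against.** The strongest reply is that the article claims less than this criticism supposes. The Discussion speaks of observing changes associated with implantation, and its next sentence names non-specific effects. On a natural reading, the implanted-but-off condition is there so that insertion and participation effects are not mistaken for stimulation effects, and the design does deliver that. This stands for the Discussion. It does not cover 'Design of the study', where the hedge concerns whether an insertion effect exists; the statement that the stagger permits its assessment is unqualified.

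Several further points stand.

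- A reader might infer that the trial will report any off-period fall as microlesioning. The documents do not say so: there is no formal test, no microlesion aim, and no analysis step that makes the attribution.
- A reader might infer that the stagger is uninformative about the implanted, unstimulated state. It is not. It extends off-stimulation observation from about four weeks to day 90 in three subjects, beside concurrent blinded stimulated subjects. Little change while off would argue against a sizeable insertion benefit, unless offset by worsening from another cause.
- New deficits on the ADIPS battery, given at baseline and monthly, are less open to the objection: placebo improvement and selection at a high CAPS would not readily produce them.
- Regression to the mean is limited by the repeat CAPS, and the required five-year illness without a six-month remission makes marked spontaneous improvement less likely.
- Individual results are to be published in full, so readers can see the off-period course.

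**Conclusion.** The point holds as a matter of identifiability. No randomised contrast contains the insertion effect, and off-stimulation change from baseline gives only insertion plus everything else that follows surgery. This rests on the described schedule and on the absence of any unimplanted or sham-surgery comparator, not on an assumed effect size. The regression figures (0.3 to 4.1 points) are illustrative, depend on assumed inputs, and show only that this component is small.

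Severity is minor. The stimulation contrast is untouched, as are the safety aim and the outcome schedule. It would go too far to infer that the two-month delay loses its justification: the same section also rests it on sham versus active stimulation, which the design does support. What fails is one stated design property, and the consequence is a risk of over-interpretation.

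**What to change.** Amend the sentence in 'Design of the study' and the matching one in the Discussion to say, in substance:

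> Symptom change from baseline while stimulators are off is a descriptive, uncontrolled observation. It reflects electrode insertion together with non-specific response, time and regression to the mean, and improvement in it will not be attributed to microlesioning. The comparison of groups A and B between days 30 and 90 estimates the effect of stimulation over and above implantation.

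The cost is wording only: no added subjects, visits, scans or procedures, and no change to the randomisation. The downside is that the trial gives up a mechanistic claim it cannot support. A comparator that could separate insertion from the rest may not be feasible in a six-subject pilot and is not needed for this correction.
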